### Minimising bias

Blinding is not possible, since we consider that giving prolonged intravenous placebo would pose an unnecessary risk to participants and therefore would be unethical. Because an open label study is at risk of bias, we have appointed an endpoint review committee to review the clinical notes relating to any patient who fulfils the criteria for a potential treatment failure. All notes reviewed are redacted for personal identifiable data and for any information that might indicate the choice and route of antibiotic therapy. The endpoint review committee is therefore blind to treatment allocation. The notes are examined against objective criteria for meeting the primary endpoint.

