### Study interventions: PO versus IV antibiotic strategy

The selection of individual antibiotic agents within the allocated strategy (that is, PO or IV antibiotics) is the responsibility of the infection specialist caring for the patient; the choice depends on microbiological assessment, the side effect profile and patient preference. In the event of a culture-negative bone or joint infection (or where there is a delay in availability of culture results), the infection specialist selects the most appropriate empiric therapy. If new information becomes available, the infection specialist may change the choice of antibiotic agent but should remain within the allocated route of administration strategy; if this is not possible, the participant will have reached an endpoint.

If randomised to IV strategy, participants are expected to complete 6 weeks of IV antibiotic therapy. Where it is common practice to use adjunctive oral agents in patients treated with IV therapy (for example, oral rifampicin as adjunctive therapy for biofilm-related staphylococcal infection), such therapy will be allowed.

If randomised to the PO strategy, participants are expected to commence PO therapy within seven days of definitive surgical management (or, if managed without surgery, from the start of antibiotic therapy for that clinical episode). If a participant allocated to the PO strategy requires IV antibiotic therapy for an unrelated intercurrent illness during the initial 6 weeks of treatment, or experiences vomiting or inability to swallow, or concerns arise about absorption of oral medication, then IV antibiotic therapy may be substituted for up to five days. If IV antibiotic prescribing exceeds five days, the patient will have met a secondary endpoint, but will still contribute to the intention-to-treat analysis.

Follow-on antibiotic treatment after the initial 6 weeks may be prescribed in either arm of the trial, but the choice of agent, duration and route of administration are not governed by the trial protocol.

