If continuing in the randomised strategy (IV or PO) is no longer compatible with optimal clinical care, the clinician must commence appropriate alternative therapy. Appropriate reasons for discontinuing the allocated treatment might include lack of suitable medication within the allocated strategy, adverse reactions, contraindications or susceptibility testing results. Failure to maintain intravenous access is an appropriate reason for discontinuing IV antibiotics. A wound discharge or other clinical signs related to the incident infection, or its apparent resolution, are not appropriate indications for changing from one treatment strategy to the other, since there is equipoise regarding efficacy.

There are no formal withdrawal criteria in this study other than at the request of a participant. All patients are free to withdraw their consent at any time; if they elect to withdraw from the allocated treatment strategy during the randomised treatment phase, they will meet a secondary endpoint but may still be followed up and be included in the analysis provided that appropriate consent is given.

Any medical decision to withdraw a participant from the randomised strategy is discussed with the chief investigator (CI) or the trial physician. Changing the antibiotic whilst remaining within the allocated strategy need not be discussed, but a clinician with appropriate training in managing infection must make such a decision.

The infection specialist may adjust dosage based on renal or hepatic function, drug interactions or other factors according to drug labelling information, the British National Formulary and local pharmacy guidelines. All antibiotics used (including dosage, route of administration and duration) are recorded from the day of randomisation through to final follow-up at one year (Fig. 1).

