#### Secondary endpoints

Secondary analyses will include: (i) a per-protocol analysis based on all participants who have received at least 4 weeks of randomised therapy and (ii) intention-to-treat and per-protocol analyses in the subgroup with “definite” or “definite”/“probable” infection at randomisation. These secondary analyses will focus on consistency of point estimates and 95 % CI, rather than formal comparison with the 7.5 % non-inferiority margin. We will similarly compare the proportions of participants with secondary endpoints, or the distributions of continuous secondary outcomes (rank sum tests). Subgroup analyses will use interaction tests to determine the consistency of treatment effects by type of infection and infecting pathogen. We record treatment intentions for both intravenous and oral routes at baseline before randomisation. Subgroup analysis will compare efficacy of intravenous versus oral antibiotic therapy according to whether or not rifampicin was used as an adjunctive therapy in the intravenous and oral arms (four subgroups). We will also conduct subgroup analyses according to the clinician’s specific antibiotic intentions, as recorded prior to randomisation.

A survival analysis will be performed to assess post-randomisation surveillance bias, which would present as a delay in time to meeting an endpoint in one randomised group. Other secondary analyses will include regression models (logistic (binary) or quantile (continuous)) to calculate estimates of treatment differences for the primary and secondary endpoints adjusted for age, comorbidity, infecting pathogen and type of surgical intervention.

The statistical analysis plan will be locked prior to analyses being undertaken and will be made freely available at the time of publication.

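### As worded, the rifampicin subgroups are formed by rifampicin given after open-label allocation, so oral versus IV within them is not a randomised comparison; baseline intention should define them

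*Protocol article*

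**What the plan says.** Three consecutive sentences under Analysis of efficacy, Secondary endpoints, carry the point.

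- The first describes a baseline variable: "We record treatment intentions for both intravenous and oral routes at baseline before randomisation".
- The second sets out the rifampicin analysis. It compares the efficacy of the two routes "according to whether or not rifampicin was used as an adjunctive therapy in the intravenous and oral arms (four subgroups").
- The third adds further subgroup analyses, by the clinician's "specific antibiotic intentions, as recorded prior to randomisation".

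Other sections show how rifampicin comes to be given.

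- Under Study interventions, the infection specialist chooses the agents. When new information arrives, "the infection specialist may change the choice of antibiotic agent but should remain within the allocated route of administration strategy".
- The same section permits add-on oral drugs in the IV arm: "Where it is common practice to use adjunctive oral agents in patients treated with IV therapy". Its example is "oral rifampicin as adjunctive therapy for biofilm-related staphylococcal infection".
- All antibiotics "are recorded from the day of randomisation through to final follow-up at one year".
- Under Minimising bias, "Blinding is not possible". Only the endpoint review committee is kept unaware of allocation.

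**The concern.** A subgroup comparison keeps the protection of randomisation only if membership is fixed before allocation, or at least cannot be affected by it. Rifampicin actually given does not meet that condition here. The prescriber knows the arm. In the oral arm rifampicin forms part of an all-oral regimen, and in the IV arm it is an oral addition to an intravenous one, so the reasons for giving it may differ. Prescribing may also respond to culture results and tolerability that emerge after randomisation. Oral-arm users and IV-arm users may therefore be different kinds of patient, and so may the two sets of non-users.

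At stake is how one secondary analysis is interpreted. Selection alone could produce an apparent route effect among users or non-users, or an apparent interaction with rifampicin, or it could hide a real one. Readers are likely to look at this analysis, because the article's Discussion singles out oral rifampicin in the IV arm as an apparent departure from allocation that needs explaining.

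**Working it through.** **Step 1. What decides membership?** The article gives no figure for rifampicin, so there is no stated number to reproduce. The check starts from the text.

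| Candidate basis for the subgroup | Fixed before allocation? | Defined identically in both arms? |
|---|---|---|
| Rifampicin given (wording of the rifampicin sentence) | No: chosen and changeable by unblinded specialists, recorded from the day of randomisation | No: each patient is seen under one arm only |
| Rifampicin intended under the IV plan and under the oral plan (sentence before it) | Yes | Yes: both plans are recorded for every patient |

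The rifampicin sentence is in the past tense. The sentence after it introduces the intention-based analyses with the word *also*, which marks them as something different. The plain reading is therefore actual use.

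**Step 2. Can selection alone create a difference?** The assumptions below are for illustration and are not in the article, apart from the overall rate.

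- Overall failure is 12.5 % (the pooled rate under Sample size).
- Half the patients are high risk (17.5 %) and half low risk (7.5 %), since (17.5 + 7.5)/2 = 12.5.
- Neither route nor rifampicin has any effect.

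Let h and l be the proportions of high-risk and low-risk patients given rifampicin in an arm. Then:

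- failure among users = (17.5h + 7.5l)/(h + l)
- failure among non-users = [17.5(1 − h) + 7.5(1 − l)]/(2 − h − l)

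Worked example, with IV h = 0.4, l = 0.2 and oral h = l = 0.5:

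- IV users: (7.0 + 1.5)/0.6 = 14.2 %. Oral users: 12.5 %. Difference −1.7 points.
- IV non-users: (10.5 + 6.0)/1.4 = 11.8 %. Oral non-users: 12.5 %. Difference +0.7 points.

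| Use in IV (high/low risk) | Use in oral (high/low risk) | Oral − IV, users | Oral − IV, non-users |
|---|---|---|---|
| 30 % / 30 % | 50 % / 50 % | 0 | 0 |
| 40 % / 20 % | 40 % / 20 % | 0 | 0 |
| 40 % / 20 % | 50 % / 50 % | −1.7 | +0.7 |
| 10 % / 30 % | 60 % / 40 % | +3.5 | −1.6 |
| 40 % / 20 % | 30 % / 50 % | −2.9 | +1.5 |

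The bias is zero when use is unrelated to prognosis, or related to it identically in both arms. Otherwise it can take either sign.

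**Step 3. A second model, with weak and strong cases shown together.** Assume logit(failure) = −2.15 + 0.8 × severity in both arms, with severity standard normal. This gives 12.7 % failure overall. Assume logit(use) = 0.2 + a × severity in the oral arm and −0.8 + b × severity in the IV arm. Again there is no true effect.

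| a (oral) | b (IV) | Users | Non-users |
|---|---|---|---|
| 0 | 0 | 0 | 0 |
| −0.3 | 0 | −1.1 | +1.3 |
| −0.6 | 0 | −2.1 | +2.5 |
| −0.6 | −0.6 | +0.9 | +1.1 |
| +0.6 | +0.6 | −1.2 | −0.9 |
| −0.6 | +0.6 | −5.4 | +4.1 |

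The last row needs severity to act in opposite directions in the two arms. Nothing in the article suggests that it does.

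**Step 4. Scale against sampling error.** With 1,050 patients there are 525 per arm. In the a = b = 0 case, use is about 55 % (oral) and 31 % (IV), so there are about 289 and 163 users. The standard error of the user contrast is √[0.127 × 0.873 × (1/289 + 1/163)] = 3.3 points. For non-users (about 236 and 362) it is 2.8 points. Most of the illustrative biases are smaller than one standard error, but a larger sample would not remove them.

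**The case against.** The strongest reply is that the authors may have meant intended use. The sentence on recorded intentions comes directly before the rifampicin sentence and seems to introduce it. The count of four also allows that reading. Arm crossed with use gives four cells, each holding one arm only. Rifampicin intended under the IV plan (yes or no) crossed with rifampicin intended under the oral plan (yes or no) gives four strata, each holding both arms. This reading is possible. But the past tense, the reference to use in the two arms, and the later *also* all point to actual use. If intention was meant, the wording still needs correcting.

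The second reply is that intention-based subgroup analyses are already planned. That is true, and a reader who inferred that the baseline data go unused would be mistaken. The article does not, however, make those analyses the basis of the rifampicin comparison, nor say that the as-used comparison is non-randomised.

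The third reply is that operational subgroup definitions belong in the statistical analysis plan, which is to be locked before analysis. The point here is not a missing detail, though. The article states a definition, and the definition it states is a weak one.

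Two stronger readings are tempting and are not supported.

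- A reader might set the simulated biases against the 7.5-point margin. The article applies that margin to the primary comparison. For the per-protocol and infection-certainty analyses it expressly disclaims formal comparison with it, and nothing applies it to the rifampicin subgroups.
- A reader might infer a sizeable immortal-time bias, because a patient who fails early has less chance to be counted as a user. The article gives no start time for adjunctive rifampicin, and the calculations above contain no time element, so no size can be claimed.

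**Conclusion.** The point holds in a limited form. As worded, the rifampicin subgroups rest on treatment received after open-label allocation, so the oral-versus-IV contrast within users or within non-users is observational and may be biased in either direction. The article does not allow the size to be derived. Under assumed selection patterns the bias runs from 0 to a few percentage points, with the largest value only under opposite-direction selection. These figures show that bias can arise; they do not estimate it.

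This should be fixed, but it does not threaten the trial's main conclusion. The primary result is the unadjusted intention-to-treat difference, and neither that analysis, nor the margin, nor the sample size depends on rifampicin subgroups. The verdict rests on the plain reading of the rifampicin sentence. If intended use was meant, the point reduces to correcting the wording.

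**What to change.** 1. Confirm that adjunctive rifampicin is among the treatment intentions recorded before randomisation. The article does not say so explicitly.
2. If it is, replace actual use by intended use. Classify every patient, whichever arm they enter, by whether rifampicin was intended under the recorded IV plan and under the recorded oral plan. The strata could be both, one or neither, or the full four-way cross if numbers allow.
3. Compare the randomised arms within each stratum, and judge consistency by a treatment-by-subgroup interaction test, as the section already does for infection type and pathogen.
4. If a table by rifampicin actually given is kept, label it descriptive and draw no conclusion about route efficacy from it. If step 1 shows that rifampicin intention was not captured, the as-used table should carry the same label.

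The cost is a change of wording in the protocol and the matching line of the analysis plan before it is locked. If step 1 is confirmed, no new data are needed, and no design figure changes.

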#### Patient adherence

We will describe patient adherence according to the Morisky scale, using data from the questionnaires (full cohort) and MEMS (sentinel sites).

#### Diagnostic subgroup definitions

The clinical diagnostic inclusion criterion means the trial reflects real-world practice, and facilitates timely entry to the study. In the analyses we will use histology, microbiology and clinical details to determine “definite” evidence of infection, as defined by: a) isolating bacteria from two or more samples of bone/spine/peri-prosthetic tissue, where the bacteria are phenotypically indistinguishable OR b) a pathogenic organism (for example, *Staphylococcus aureus* but not *Staphylococcus epidermidis*) on a single, closed biopsy of native bone or spine OR c) diagnostic histology on bone/peri-prosthetic tissue OR d) a draining sinus tract arising from bone/prosthesis or OR e) frank pus adjacent to bone/prosthesis.

If any of these criteria are met, then the category “definite” infection is applied without independent review.

Where these criteria are not met, the review committee members are sent a redacted copy of the patient’s admission notes and laboratory results from the time of randomisation, and apply the following criteria to determine “probable” or “possible” infection.

Infection is categorised as “probable” where microbiological sampling has not been undertaken, plus none of the other criteria for definite infection are fulfilled and any one of the following are met:Radiological or operative findings of periosteal changes suggesting chronic osteomyelitisRadiological findings suggesting discitis/spinal infectionDevelopment of a discharging wound after an orthopaedic procedure where prosthetic material has been implantedPresence of deep pus close to but not adjacent to bone/prosthetic joint/orthopaedic devicePresence of peri-prosthetic necrotic boneRapid loosening of a joint prosthesis/orthopaedic device (that is, leading to localised pain in less than 3 months since implantation) in the absence of a mechanical explanation for rapid loosening.

Infection is categorised as “possible” where microbiological sampling has been undertaken with negative results (according to criteria described above for “definite” infection) plus other criteria for definite infection are not fulfilled and, in addition, one or more of the criteria listed a) to f) above is met. The review committee members are blinded to treatment allocation and subsequent outcome. Secondary analysis will evaluate non-inferiority for “definite” or “definite”/“probable” infections only.

### Health economic analysis

The health economic evaluation has two parts. The first, a within-trial analysis, will be performed based on the resource use and health-related quality of life (EQ-5D-3 L) data. We will use the British National Formulary for antibiotic costs (with a sensitivity analysis for hospital pharmacy discounts). We will include the costs associated with IV administration based on staffing requirements, equipment cost, clinic visits and transport costs for patient visits as observed in the trial. For unplanned inpatient stays and additional outpatient attendances other than those related to IV administration, we will use standard NHS reference costs.

We will calculate mean costs in each arm of the trial and differences in costs between the two arms, with 95 % confidence intervals. The EQ-5D-3 L instrument will be used to estimate per-patient quality-adjusted life years (QALY) with adjustment for any differences between the groups in EQ-5D-3 L at baseline. Non-parametric bootstrapping techniques will be employed to confirm the robustness of the statistical analysis of cost, QALY and cost per QALY. Uncertainty in cost-effectiveness will be represented on the cost-effectiveness plane and as confidence intervals for cost-effectiveness ratios, or as cost-effectiveness acceptability curves, as appropriate.

The second part of the analysis will be to extrapolate the observed results in OVIVA beyond the clinical trial, in order to explore the potential lifetime cost-effectiveness of a switch in antibiotic administration route strategy. This extrapolation will be made in each diagnostic group, using estimates of long-term recurrence from the literature and the observed recurrence rates observed within the period of the trial. We will also use the published longer term costs associated with disability in order to reflect the consequences of treatment failure that persist beyond the end of the trial. Taking these estimates together, we will extrapolate the costs beyond the period of observation within the year of follow-up in the trial. This will necessarily involve a series of assumptions in applying estimates from the literature, and extensive sensitivity analyses will be examined in order to explore the robustness of the estimates.

### Trial management and quality assurance procedures

The study is conducted in accordance with the current approved protocol, International Conference on Harmonisation (ICH) Good Clinical Practice guideline, relevant regulations and standard operating procedures, including data protection.

We undertake remote monitoring of data entered in real time on a secure, anonymised database and conduct monitoring visits of collaborator sites to confirm integrity of data.

### Data monitoring committee

The DMC is composed of three members, two of whom are specialists in infectious diseases and the other a senior statistician. None are involved in recruitment, randomisation or follow-up for trial participants or contribute to the trial in any way other than through the DMC. The DMC met to discuss the study design and standard operating procedures shortly before the start of the study. The DMC evaluate the frequency of endpoints in an unblinded analysis annually in a closed meeting and make recommendations to the trial steering committee. Although the DMC may recommend suspension or cessation of the trial at any time, it is expected that they would only recommend early stopping if there was a very significantly worse outcome in the PO antibiotic group as compared to the IV group, as determined for example by the Haybittle-Peto stopping boundary.

### Trial steering committee

The trial steering committee (TSC) consists of two independent co-chairs ([name], Imperial College London and [name], Health Protection England), two public/patient group representatives ([name], Nuffield Orthopaedic Centre Network and [name], Healthcare-Associated Infection Service Users Research Forum), and the chief investigator, supported by the trial physician, coordinator and statistician.

The TSC met first at the start of the trial, and then meets yearly to review recruitment rates, protocol amendments, and any protocol deviations identified. The co-chairs of the TSC receive recommendations directly from the DMC and may make recommendations to the sponsor regarding the running of the trial.

### Ethical considerations

All clinicians involved in the study have acknowledged a position of equipoise in relation to route of antibiotic therapy for treatment for bone and joint infections; they accept that there is currently insufficient evidence to determine whether oral antibiotics are inferior (or superior) to intravenous antibiotics in this context. This uncertainty is conveyed to patients both verbally and in writing. All investigators have agreed that they will ensure that this study is conducted in full conformity with relevant regulations and with the ICH Guidelines for Good Clinical Practice (CPMP/ICH/135/95) July 1996. The trial is in full compliance with the Helsinki Declaration and received a favourable ethical opinion from the Health Research Authority through the NRES Committee South Central - Oxford B (REC reference 13/SC/0016).

